**Methods:**

A randomised effectiveness trial with an economic evaluation in primary care with 158 patients aged 18 years and older who are frequently consulting their GP with MUS. Patients will be assigned to psychosomatic therapy in addition to usual care or usual care only. Psychosomatic therapy is a multi-component and tailored intervention, aiming to empower patients by applying psycho-education, relaxation techniques, mindfulness, cognitive approaches and/or graded activity. Patients assigned to the psychosomatic therapy receive 6 to 12 sessions of psychosomatic therapy, of 30–45 min each, delivered by a specialised exercise or physical therapist.

Primary outcome measure is patient-specific functioning and disability, measured with the Patient-Specific Functional Scale (PSFS). Secondary outcome measures are symptom severity, consultation frequency and referrals to secondary care, patient satisfaction, quality of life and costs. Assessments will be carried out at baseline, and after 4 and 12 months.

An economic evaluation alongside the trial will be conducted from a societal perspective, with quality-adjusted life years (QALYs) as outcome measure. Furthermore, a mixed-methods process evaluation will be conducted.

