Illness beliefs are measured with the brief Illness Perception Questionnaire (IPQ-B) [39]. A higher score reflects a more threatening view of the illness. The IPQ-B is based on the revised IPQ-R [40] and designed to assess the cognitive and emotional representations of illness. It consists of nine items in total. Six items assess cognitive illness representations: consequences, timeline, personal control, treatment control, identity and comprehension of illness. One item reflects emotional representation, one item assesses a combination of emotional and cognitive representation: concern. The score will be rated on an 11-point scale, ranging from 0 (not at all) to 10 (very much). The last item is an open-question to assess causal representation.

The GP will be asked to report the total number of consultations of the patient in the year after the psychosomatic therapy.

All other medical consumption will be measured with the iMTA Medical Consumption Questionnaire (iMCQ) [41]. This questionnaire measures all relevant health care-related costs like outpatient visits at any medical specialist, hospitalisations and imaging procedures.

Productivity losses due to illness or recovery will be estimated based on patient-reported absences from paid labor measured with the iMTA Productivity Cost Questionnaire (iPCQ) [41, 42]. For all secondary outcome measures we will measure mean change from baseline at 4 and 12 months’ follow-up.

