### Recruitment of study participants

The patients will be recruited from general practices participating in the Academic Network of General Practices of the VU Medical Center (ANH-VUmc), the Academic General Practices Network Academic Medical Center (AHN-AMC) and the Radboud University Medical Center Academic General Practices Network (Radboudumc-AHN). If the number of inclusions from these networks of general practices proves to be insufficient we will approach other general practices in the Netherlands (in and around Amsterdam and Nijmegen).

Eligible patients will be identified by a search strategy that selects from the electronic medical records those patients (aged 18 to 80 years) who visited their GP frequently over the past 2 years with MUS, based on a list of 23 unexplained physical complaints composed by Robbins et al. [27]. Patients who visited their GP twice or more in the past months with one or more Robbins List symptoms are eligible. Table 1 presents the Robbins List with 23 physical complaints. The GP will screen the selected list of this frequently attending group patients for potential exclusion criteria and/or other pertinent reasons for not inviting them, such as a terminal disease or insufficient understanding of the Dutch language. In addition to the search strategy, participating GPs will be asked to enrol eligible MUS patients who are not present on the selected list. The identified and screened potential participants not meeting exclusion criteria will be approached by their GP who sends them a package containing a letter with brief information about the study, the PHQ-15, a brief consent form to receive more information about the study and an addressed return envelope. The PHQ-15 is a frequently used and validated questionnaire about physical symptoms [29]. It consists of 15 items, each of which can be scored from 0 (‘not bothered at all’) to 2 (‘bothered a lot’), which results in a total score ranging from 0 to 30. Higher scores indicate higher somatic symptom severity. Scores of 5, 10 and 15 represent cut-off points for low, medium and high somatic symptom severity, respectively [28].

**Table 1 Tab1:** Symptoms from the Robbins List [27]

1. Back pain	
2. Joint pain	
3. Extremity pain	
4. Headaches	
5. Weakness	
6. Fatigue	
7. Sleep disturbance	
8. Difficulty concentrating	
9. Loss of appetite	
10. Weight change	
11. Restlessness	
12. Thoughts slower	
13. Chest pain	
14. Shortness of breath	
15. Palpitations	
16. Dizziness	

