#### Effect evaluation

##### Effectiveness of the intervention

Differences in the change scores between the intervention group and the control group on the primary and secondary outcomes will be analysed with multilevel (mixed-model) linear regression analyses taking all three measurements into account (baseline, and at 4 and 12 months). We will use a model with a random intercept and all other variables fixed.

A sensitivity analysis will be performed by replacing missing values by multiple imputation. *P* values < 0.05 are considered statistically significant.

Differences in the change scores between the cohort study group and both the intervention group and the control group on the primary, secondary and other study parameters will be analysed with multilevel (mixed-model) linear regression analyses, taking all three measurements into account. We will perform subgroup analyses for severity, duration and number of the symptoms and comorbidity to explore which patients are most likely to benefit from the intervention.

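### GP consultation frequency falls under a change-from-baseline rule at 4 and 12 months, but the only count described is one follow-up total, so the stated analysis cannot be run for it

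*Protocol article*

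**What the plan says.** Consultation frequency is treated as an outcome in several places of the protocol article. The abstract (Methods) lists it: "Secondary outcome measures are symptom severity, consultation frequency and referrals to secondary care, patient satisfaction, quality of life and costs". The Introduction makes fewer consultations part of the aim. Sample size and power calculation says that the planned number also suffices for a difference of 3 consultations with an SD of 4.

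The Secondary outcomes section gives the source of the data: "The GP will be asked to report the total number of consultations of the patient in the year after the psychosomatic therapy". It assigns all other medical consumption to the iMCQ. It then closes with a rule that has no exception: "For all secondary outcome measures we will measure mean change from baseline at 4 and 12 months’ follow-up".

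Effectiveness of the intervention applies the matching model. It covers "Differences in the change scores between the intervention group and the control group on the primary and secondary outcomes", and these "will be analysed with multilevel (mixed-model) linear regression analyses taking all three measurements into account (baseline, and at 4 and 12 months". No outcome is exempted there either.

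**The concern.** The rule and the model both need a value at baseline, at 4 months and at 12 months. The described collection gives one number per patient, obtained after the fact. A total over a year cannot be split into a 4-month and a 12-month value, and it contains no baseline.

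At stake is an outcome that the article names in its aim and in its detectability claim. As written, its prespecified analysis cannot be carried out, so the actual analysis would have to be chosen later. Allocation and blinding says that the data analysts will know the assignments, so it is better to settle that choice in advance. The trial would also be unable to report a change in attendance, and could not adjust for chance differences in prior attendance between arms. Randomisation is stratified by region only.

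**Working it through.** **1. Values required against values described**

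| Time point | Needed by the rule and the model | Described for GP consultations |
|---|---|---|
| Baseline | yes | none |
| 4 months | yes | none |
| 12 months | yes | one total over a year of follow-up |

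Three other places might supply the missing values:
- The iMCQ is assigned to consumption other than the GP-reported consultations, so on the text it does not provide GP visits.
- The baseline data section lists demographic and symptom items, with no consultation count.
- The record search under Recruitment of study participants finds patients "who visited their GP frequently over the past 2 years with MUS". It is a selection step and is not named as a baseline measure.

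Even if a baseline count were recovered from the records, the single follow-up total would still leave no 4-month value. The model as written would remain short of one measurement.

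**2. The plan's own sample size**

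Inputs from Sample size and power calculation: difference 1, SD 2, alpha 0.05 (taken as two-sided), power 0.80, dropout 20%.

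- n per arm = 2 × (1.96 + 0.8416)² × 2² / 1² = 62.8, rounded up to 63.
- 63 / 0.80 = 78.75, rounded up to 79. This reproduces the stated 79 per arm.

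**3. Is the detectability claim for consultations affected?**

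Inputs: difference 3, SD 4, single follow-up total, no baseline.

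- n per arm = 2 × 7.849 × 16 / 9 = 27.9, rounded up to 28 evaluable; 28 / 0.80 = 35 recruited.
- SE with 63 evaluable per arm = 4 × √(2/63) = 0.713.
- Power = Φ(3/0.713 − 1.96) = Φ(2.25) = 0.988.

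The claim holds without a baseline count.

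**4. Precision forgone**

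With a baseline covariate that has correlation r with the outcome, SE = 0.713 × √(1 − r²). The documents give no r; 0.5 and 0.7 are assumptions.

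- r = 0.5: 0.713 × 0.866 = 0.617, 13% smaller.
- r = 0.7: 0.713 × 0.714 = 0.509, 29% smaller.

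**5. Covariate or change score, if a baseline count is added**

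This takes SD 4 at both times and 63 per arm. The SD of change is 4 × √(2(1 − r)); the SD after covariate adjustment is 4 × √(1 − r²).

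| Assumed r | SD of change | Power, change | SD, covariate | Power, covariate |
|---|---|---|---|---|
| 0 | 5.66 | 0.845 | 4.00 | 0.988 |
| 0.3 | 4.73 | 0.945 | 3.82 | 0.993 |
| 0.5 | 4.00 | 0.988 | 3.46 | 0.998 |
| 0.7 | 3.10 | above 0.999 | 2.86 | above 0.999 |

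Below r = 0.5, a change score is less precise than ignoring the baseline. The covariate is never less precise than either in this calculation.

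**The case against.** The list that opens the Secondary outcomes section names symptoms, health status, quality of life, health anxiety, illness behaviour and illness beliefs, and omits consultations. The change-from-baseline sentence could therefore be read as meant for the questionnaires only. That is a fair account of how the sentence may have arisen. It does not remove the mismatch: the abstract calls consultation frequency secondary, its data source is described in the same section, the sentence says all, and the model makes no exception.

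A second objection is that the article condenses a longer protocol, which may name a baseline count. This stands as a limit on wording: no baseline count is described, which is not the same as none existing. A reader might infer that no pre-randomisation value exists, or that the recruitment count is thrown away. The article says neither, and prior visits are in records that the practices already search. The objection does not rescue the analysis as written, because the article fixes a rule that its described data cannot meet.

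A third objection is that little harm follows, and most of this stands. A reader might infer that selecting frequent attenders biases the treatment effect through regression to the mean. It does not: counts may fall in both arms, and under randomisation that fall cancels in expectation from the between-arm contrast. Nor does the detectability claim fail. The covariate improves precision and handles chance imbalance; it does not repair a biased comparison. The documents also do not show how strongly prior attendance predicts later attendance.

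**Conclusion.** The point holds in a limited form. For GP consultation frequency, the change-score rule and the three-measurement model cannot be applied to the one follow-up total that is described. The consequences are a prespecified analysis that cannot be executed, no reportable change for this outcome, and forgone precision of 13% to 29% in the standard error at assumed correlations of 0.5 to 0.7.

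The sample size and the primary PSFS analysis are untouched. A between-arm comparison of follow-up totals remains unbiased, with power of about 99%. That statement assumes the article's difference of 3 and SD of 4, 63 evaluable patients per arm, and a counting window that is the same in both arms. The article's window is tied to the therapy, which the usual-care arm does not receive during the study. That is a separate matter, but it has to be settled in the same sentence.

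**What to change.** - In Secondary outcomes and in Effectiveness of the intervention, exempt GP consultation frequency from the change-score rule and the three-measurement model.
- State that the follow-up count will be compared between arms over one window defined identically for both, and name the model in advance.
- Use as covariate the all-cause number of GP consultations over a period of the same length before randomisation, extracted from the GP electronic record in both arms. Include patients whom the GP enrolled outside the search list.

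The cost is two or three sentences of text and a short additional record extraction per practice. The recruitment query will not do by itself: it selects visits for symptoms on the 23-item list in Table 1, whereas the outcome is the total number of consultations, and it may hold no count for patients added by the GP. Patients have no extra burden, and the sample size stays at 79 per arm.

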#### Process evaluation

We will conduct a process evaluation with quantitative and qualitative methods (mixed-methods) [25]. The process evaluation will be limited to the patients in the intervention arm and the participated therapists.

##### Quantitative data

Patients of the intervention group will be asked after the last session about their perceived recovery and satisfaction with the psychosomatic therapy. These are measured with the Global Perceived Effect scale (GPE) on a seven-point Likert scale (from completely recovered to worse than ever and from absolutely satisfied to absolutely unsatisfied) [43]. After the first and last sessions of psychosomatic therapy, patients will receive the Session Rating Scale Dutch version (SRS V.3.0). This questionnaire is a four-item visual analogue instrument with four interaction elements. First, a relationship scale rates the session on a continuum from ‘I did not feel heard, understood and respected’ to ‘I felt heard, understood and respected’. Secondly, a goals and topics scale rates the session on a continuum from ‘We did not work or talk about what I wanted to work on or talk about’ to ‘We worked on or talked about what I wanted to work on or talk about.’ The third element requires the participant to rate the session on a continuum from ‘the therapist’s approach is not a good fit for me’ to ‘the therapist’s approach is a good fit for me.’ Finally, and reiterating, the fourth scale looks at how the participant perceives the session in total along the continuum: ‘there was something missing in the session today’ to ‘overall, today’s session was right for me’ [44].

After the first and last sessions of the psychosomatic therapy, the therapeutic alliance will be assessed with the Working Alliance Inventory-Short Form (WAI-SF). The WAI-SF is a shortened version [45] of the Working Alliance Inventory (WAI). It is a widely used 12-item questionnaire that measures the strength of the therapeutic alliance in an ongoing client-therapist interaction. It comprises 12 items that are scored on a five-point Likert scale, ranging from ‘never or rarely’ to ‘very often’ [46].

All participating therapists will be asked to register, per patient, at the end of the treatment: (1) which psychosomatic therapy elements are actually applied; (2) how often these therapy elements are used and (3) the number, timing and start and end date of psychosomatic therapy sessions per patient.

##### Qualitative data

Patients who decline to participate in the study will be asked for their reasons for non-participation. Qualitative data will be collected through interviews by a research team member with 15 to 30 patients, until saturation of the data, in the psychosomatic therapy condition. To examine the patients’ experiences with the psychosomatic therapy, they will be interviewed after the psychosomatic therapy and 1 year later. We will select these patients by applying a purposive sampling strategy taking variation in, e.g. gender, age, region, symptom intensity and symptom interference into account [47]. The first interview will be done face to face within a month after ending the psychosomatic therapy and will focus on the experiences during the psychosomatic therapy and the effects on symptoms. The second face-to-face interview will be conducted a year later and will consist of only two questions: *(1) How are you now?* and *(2) What did you learn from the psychosomatic therapy?* We will encourage the patients to talk freely about their experiences with the psychosomatic therapy and their symptoms. Both interviews will last between 25 and 45 min.

In addition to the interview data, we will use written evaluations of all patients who have attended psychosomatic therapy. After their last session they will be asked to write down what they have learnt.

We will interview all 26 participating therapists after the last session of their first, second or third patient. These interviews examine the therapists’ experiences with the psychosomatic therapy elements and their reasons for choosing specific therapy elements. The questions will focus on (1) which elements are actually applied for which reasons in which patients with MUS according to psychosomatic therapists; (2) what are, according to the psychosomatic therapists, the barriers and facilitators in psychosomatic therapy for patients with MUS. In addition, we will use audio recordings of the sessions to gain understanding in the therapists’ considerations about applying the different elements of the therapy. Each interview will last between 25 and 45 min.

All interviews, both the interviews with the patients as well as the interviews with the therapists, will use a topic list as guidance. The topic list will be developed based on the aim of our study, prior research and patients’ and therapists’ feedback during the CORPUS study. Additionally, to systematically evaluate the experiences with the psychosomatic therapy, we will add topics based on the framework described by Saunders et al. [26]. Based on the topic list, an interview guide with semi-structured, open-ended questions will be formulated and pilot tested in three patients.

All interviews of the participating patients and the therapists will be audio recorded (with consent), transcribed verbatim, anonymised and analysed.

### Participant timeline

An overview of enrolments, assessments and the time of collection within the trial can be found in Fig. 1.

### Sample size and power calculation

The main aim of our study is to establish whether, compared to usual care, psychosomatic therapy improves daily functioning, disability and symptoms, while reducing costs.

Calculations of sample size are based on a minimally relevant difference (mrd) between the two arms of 1 point on the PSFS (range 0–10) [32], with a standard deviation (sd) of 2 points, with an alpha of 0.05 and a power of 0.80. With an estimated dropout rate of 20% after 1 year at least 79 patients per treatment arm need to be included. With this sample size, we can also detect differences in perceived symptom severity (measured on a visual analogue scale (VAS); mrd = 1.3; sd = 2.6) and number of consultations (mrd = 3; sd = 4).

### Recruitment of study participants

The patients will be recruited from general practices participating in the Academic Network of General Practices of the VU Medical Center (ANH-VUmc), the Academic General Practices Network Academic Medical Center (AHN-AMC) and the Radboud University Medical Center Academic General Practices Network (Radboudumc-AHN). If the number of inclusions from these networks of general practices proves to be insufficient we will approach other general practices in the Netherlands (in and around Amsterdam and Nijmegen).

Eligible patients will be identified by a search strategy that selects from the electronic medical records those patients (aged 18 to 80 years) who visited their GP frequently over the past 2 years with MUS, based on a list of 23 unexplained physical complaints composed by Robbins et al. [27]. Patients who visited their GP twice or more in the past months with one or more Robbins List symptoms are eligible. Table 1 presents the Robbins List with 23 physical complaints. The GP will screen the selected list of this frequently attending group patients for potential exclusion criteria and/or other pertinent reasons for not inviting them, such as a terminal disease or insufficient understanding of the Dutch language. In addition to the search strategy, participating GPs will be asked to enrol eligible MUS patients who are not present on the selected list. The identified and screened potential participants not meeting exclusion criteria will be approached by their GP who sends them a package containing a letter with brief information about the study, the PHQ-15, a brief consent form to receive more information about the study and an addressed return envelope. The PHQ-15 is a frequently used and validated questionnaire about physical symptoms [29]. It consists of 15 items, each of which can be scored from 0 (‘not bothered at all’) to 2 (‘bothered a lot’), which results in a total score ranging from 0 to 30. Higher scores indicate higher somatic symptom severity. Scores of 5, 10 and 15 represent cut-off points for low, medium and high somatic symptom severity, respectively [28].

**Table 1 Tab1:** Symptoms from the Robbins List [27]

1. Back pain	
2. Joint pain	
3. Extremity pain	
4. Headaches	
5. Weakness	
6. Fatigue	
7. Sleep disturbance	
8. Difficulty concentrating	
9. Loss of appetite	
10. Weight change	
11. Restlessness	
12. Thoughts slower	
13. Chest pain	
14. Shortness of breath	
15. Palpitations	
16. Dizziness	
17. Lump in throat	
18. Numbness	
19. Nausea	
20. Loose bowels	
21. Gas or bloating	
22. Constipation	
23. Abdominal pain	

Patients interested in participating in the study, who return the signed brief consent form and the questionnaire, and have a PHQ-15 score of 5 or higher are potentially eligible. They will receive extensive study information, an informed consent form and a return envelope. Patients will be allowed a period of at least 2 weeks to consider their decision on participation in the study. During this period, the researcher will be available to answer any questions that might arise by telephone or e-mail. To participate, the patient will be asked to sign the informed consent form and return it to the researcher. After the signed informed consent form has been received, an e-mail will be sent to the participant with a link to the web-based baseline measurement. In case the patient prefers a paper version of the questionnaires, this will be sent by regular mail.

Patients who do not consent to randomisation (e.g. due to a strong preference for one of the treatment options), will be invited to participate in a parallel cohort study alongside the trial to monitor outcome in this group of patients.

During monthly meetings, the Steering Committee, comprised of two coordinating investigators, the researcher and two methodologists, will monitor the recruitment progress. If the recruitment is suboptimal, the Steering Committee will recommend to approach and add new study sites. The Steering Committee will be responsible for managing all study sites.

According to the local standards of the Medical Ethics Committee of VU University Medical center a data monitoring committee (DMC) is not needed because of the assumed minimal risks of the intervention and short duration of the recruitment and trial. Participating GPs and participating psychosomatic therapists wil remain responsible for the medical situation of their patients. They will report serious adverse events (SAEs) to the coordinating investigators ([name] and [name]). The coordinating investigator ([name]) is responsible for reporting SAEs to the accredited METC. SAEs are not expected as the risk of such events as a consequent of participating in this study is extremely low. For above mentioned reasons we also have not planned any interim analyses.

Within the research center, only internal audits will take place. It is not yet known whether our trial will be subject to this.

